#### Safety

Safety analyses will be carried out on the Safety Set.

- Adverse events

Number of adverse events, number and percentage of patients reporting at least one adverse event will be described by System Organ Class and Preferred Term, by treatment group and overall. The same analysis will be performed for emergent adverse events and serious adverse events.

- Hypoglycaemia, oedema and cardiovascular events:

A survival analysis will be performed in case of sufficient number of events.

- Clinical laboratory evaluation

Laboratory parameters will be described by group for the safety set using value at the visit, last value under treatment and change from baseline to last value under treatment.

Moreover, biochemistry and haematology parameters will be classified according to the laboratory reference ranges and alert values for the potentially clinically significant abnormal values, and shift tables from baseline to first event will be presented.

- Vital signs

Vital signs will be described by group using value at the visit, last post-baseline value and change between baseline and last post-baseline value.

Moreover, blood pressure and heart rate will be classified according to the abnormal low and high values.

- ECG

ECG abnormalities will be described.

- Echocardiography

Centralised LVEF will be described by group using value at the visit, last post-baseline value and change between baseline and last post-baseline value. Moreover centralised echocardiography abnormalities will be described.

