**The following safety laboratory assessments will be performed:**

- Standard haematology: red blood cell count, red blood cell indexes, white blood cell count, differential white blood cell count, blood smears, platelet count. They will be assessed at each visit and in case of premature discontinuation.
- Biochemistry
  - o Total proteins, creatinine, albumin, sodium, potassium, chlorides calcium, total bilirubin, alkaline phosphatase. They will be assessed at W0, W28 and W52 and in case of premature discontinuation.
  - o Lactic acid and uric acid will be assessed at W0, W52 and in case of premature discontinuation.
- NT-proBNP will be assessed centrally at W0, W28, W52, in case of premature discontinuation and in case of oedema (to evaluate an underlying heart failure).

**Liver enzymes** (ALAT, ASAT,  $\gamma$ -GT) will be assessed at W0, W4, W8, W16, W28, W40, W52 and in case of premature discontinuation.

- **If ALAT level is > 2.5 times the upper normal limit prior to inclusion, the patient should not be included.**
- **If ALAT level is > 3 times the upper normal limit after inclusion,** a re-test should be performed within 7 days. If the value remains 3 times the normal upper limit, the study treatment will be stopped and the patient withdrawn.
- **In case of unexplained symptoms suggestive of hepatic disease** (nausea, vomiting, abdominal pain, fatigue, loss of appetite, jaundice, dark urines), complete liver function tests should be performed. Until the results are obtained, the decision to maintain study treatment will relay on clinical judgement. In case of jaundice, the study treatment will be discontinued.

**Haemoglobin and haematocrit will be assessed** at every visit and in case of premature discontinuation.

- **If, at inclusion, haemoglobin level is < 12g/dL in men and < 11g/dL in women, the patient should not be included.**
- **If, after inclusion, clinically significant anaemia** is detected, see appendix 12.

The results (with the clinical assessment of the investigator) will be included in the CRF and one copy kept in the patient file. The investigator will report in the adverse event section of the CRF the abnormal biological parameters **only** if considered as clinically significant and not already reported/considered as pre-existing conditions without aggravation.

- **Body weight, heart rate, blood pressure, ECG and echocardiography:**

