**Monitoring of liver function:**

There have been rare reports of hepatocellular dysfunction during post-marketing experience (see section 4.8). It is recommended, therefore, that patients treated with pioglitazone undergo periodic monitoring of liver enzymes. Liver enzymes should be checked prior to the initiation of therapy with pioglitazone in all patients. Therapy with pioglitazone should not be initiated

in patients with increased baseline liver enzyme levels (ALT > 2.5 X upper limit of normal) or with any other evidence of liver disease.

Following initiation of therapy with pioglitazone, it is recommended that liver enzymes be monitored periodically based on clinical judgement. If ALT levels are increased to 3 X upper limit of normal during pioglitazone therapy, liver enzyme levels should be reassessed as soon as possible. If ALT levels remain > 3 X the upper limit of normal, therapy should be discontinued. If any patient develops symptoms suggesting hepatic dysfunction, which may include unexplained nausea, vomiting, abdominal pain, fatigue, anorexia and/or dark urine, liver enzymes should be checked. The decision whether to continue the patient on therapy with pioglitazone should be guided by clinical judgement pending laboratory evaluations. If jaundice is observed, drug therapy should be discontinued.

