**Haematology:**

There was a small reduction in mean haemoglobin (4 % relative reduction) and haematocrit (4.1 % relative reduction) during therapy with pioglitazone, consistent with haemodilution. Similar changes were seen in metformin (haemoglobin 3 - 4 % and haematocrit 3.6 – 4.1 % relative reductions) and to a lesser extent sulphonylurea (haemoglobin 1 – 2 % and haematocrit 1 – 3.2 % relative reductions) treated patients in comparative controlled trials with pioglitazone.

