#### 4.8 Undesirable effects

The following adverse reactions were observed: gastrointestinal disorders (nausea, vomiting, stomach pain, diarrhea), asthenia, confusion, drowsiness or dizziness. These effects are

mainly observed at dosages higher than 3 tablets per day. Individual susceptibility has also been observed.

Very rare cases of **anaphylactic** reactions have been reported: hypotension, shock, rash, urticaria, Quincke oedema.

Increase in hepatic enzymes and hepatitis (very rare) have also been reported.

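### The laboratory shift tables stop at an undefined first event instead of the worst value under treatment, so they can understate the worst grade a patient reached

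*Protocol*

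**What the plan says.** Protocol section 14.1.4, under Safety, Clinical laboratory evaluation, plans three things for the Safety Set.

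- Laboratory parameters are described by group "using value at the visit, last value under treatment and change from baseline to last value under treatment".
- Biochemistry and haematology parameters are also "classified according to the laboratory reference ranges and alert values for the potentially clinically significant abnormal values".
- In the same sentence as that classification, "shift tables from baseline to first event will be presented".

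The section does not say what counts as an event, and it names no summary of the worst value under treatment.

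Section 12.2 sets the sampling. Liver enzymes "will be assessed at W0, W4, W8, W16, W28, W40, W52 and in case of premature discontinuation". For standard haematology, "They will be assessed at each visit and in case of premature discontinuation".

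**The concern.** A shift table is normally read as showing how far each patient moved from baseline. With repeated samples and more than one level of abnormality, the first abnormal value need not be the worst. A patient who leaves the reference range slightly at W8 and reaches an alert value at W28 has a worst grade of alert. A table that closes at the first out-of-range value files that patient as mild.

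The parameters affected are ones the protocol has reason to watch. For pioglitazone the appended product text says "There have been rare reports of hepatocellular dysfunction during post-marketing experience", and it also describes a small fall in mean haemoglobin consistent with haemodilution. For benfluorex the appended text says "Increase in hepatic enzymes and hepatitis (very rare) have also been reported". The safety profile is a stated secondary objective, and this is the only table named in the section that relates a patient's baseline class to a later class.

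**Working it through.** **No plan figure to reproduce.** The protocol gives no expected frequency of laboratory abnormalities, no distribution and no list of alert limits. The check is therefore a reading of the text, followed by an illustration on assumed values.

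**Step 1: can the first and the worst value differ?** Section 12.2 gives post-baseline liver samples at W4, W8, W16, W28, W40 and W52. That is six, plus one at premature discontinuation. Section 14.1.4 gives at least two levels of abnormality: outside the reference range, and alert. So they can differ.

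**Step 2: what does the undefined term allow?**

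| Reading of first event | Patient mild at W8, alert at W28 is shown as |
|---|---|
| First value outside the reference range | mild |
| First value in the alert class | alert |
| First occurrence in each class | both classes |

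Only the first reading hides the later grade. On the second, the table still shows the first alert value, which may not be the worst one.

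**Step 3: do the other named outputs show the worst grade?**

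- *Value by visit, last value, change to last value.* A peak that resolves is absent from the last value, and group summaries by visit do not show each patient's worst grade.
- *Alert-value classification.* It counts every alert-level patient if it uses all values under treatment. The section does not say whether it does.
- *Withdrawal for ALAT.* Sections 9.6.1 and 12.2 require a confirmed rise above 3 times the upper limit of normal (ULN). An unconfirmed peak does not stop treatment.
- *Withdrawal for anaemia.* Section 9.6.1 and Appendix 12 require both a low haemoglobin and a minimum fall. Take a man going from 13.3 to 11.9 g/dL. He is below 12 g/dL, but the fall is 13.3 − 11.9 = 1.4 g/dL, short of the 1.5 g/dL in the rule.
- *Adverse events.* Section 12.2 has abnormal values reported only if the investigator considers them clinically significant.

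**Step 4: illustration for ALAT on the first reading.** All inputs are assumptions, none from the protocol: log-normal ALAT with median 0.6 ULN and log-scale SD 0.55, six visits, mild above 1 ULN, alert above 3 ULN, and within-patient correlation 0, 0.5 or 0.8. Each case was run without a trend, and with 5% of patients rising by 0.15 log units per visit (by the sixth visit, a factor of e^0.9 ≈ 2.46). Each scenario has 400,000 simulated patients. The quantity is the share of patients ever at alert whose first out-of-range value came earlier and was mild.

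| Correlation | Trend | Ever at alert | Shown as mild |
|---|---|---|---|
| 0 | none | 1.02% | 34.8% |
| 0 | 5% rising | 2.00% | 58.4% |
| 0.5 | none | 0.90% | 73.6% |
| 0.5 | 5% rising | 1.66% | 84.3% |
| 0.8 | none | 0.62% | 71.0% |
| 0.8 | 5% rising | 1.19% | 85.1% |

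The first row can be checked by hand.

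- Out of range at one visit: P(Z > −ln 0.6 / 0.55) = P(Z > 0.929) = 0.1765.
- Alert at one visit: P(Z > ln(3/0.6) / 0.55) = P(Z > 2.926) = 0.001715.
- Ever at alert: 1 − (1 − 0.001715)^6 = 0.01025.
- First out-of-range value is itself alert: (0.001715/0.1765) × [1 − (1 − 0.1765)^6] = 0.00972 × 0.688 = 0.00669.
- Shown as mild: 1 − 0.00669/0.01025 = 34.7%, in line with the simulated 34.8%.

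On the alert reading the share is 0% by definition. The ALAT stopping rule does not alter these shares, because they depend only on values up to the first alert value.

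**The case against.** The case against is substantial.

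- *The term is open.* The words just before it concern alert values, so first event can fairly be read as the first alert-level value. The problem then disappears. **This stands**, and it is why the lower end of the range is 0%.
- *The definition belongs in the statistical analysis plan.* Section 14.1 leaves implementation detail to that plan, which is not shown and may settle the term. **This stands in part.** The definition of an event can wait for it. The choice of first over worst, however, is made in the protocol, and section 14.1 says the analysis plan follows the protocol's principal features.
- *Serious cases surface elsewhere.* A confirmed ALAT rise or anaemia stops treatment, section 9.6.2 asks for full biology at that point, and confirmed anaemia must be reported as an adverse event. **This stands for many patients.** It does not cover unconfirmed or resolving ALAT peaks, or haemoglobin falls that miss the two-part rule. No other output is sure to show these by grade.
- *The magnitude is invented.* **This stands.** The percentages show that the reading matters and do not forecast this trial.

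A reader might infer that the trial as a whole under-reports hepatic and haematological harm, or does so more in one arm. The documents do not support that. The loss is limited to one table. The adverse-reaction section of the benfluorex text lists hepatic effects but no haematological ones. Nothing in the protocol shows that the time course of abnormalities differs between arms.

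**Conclusion.** The concern holds in a limited form. The protocol fixes the shift table at a first event, leaves that term undefined, and names no shift to the worst value under treatment. If the event is the first value outside the reference range, the table can understate the worst grade reached; if it is the first alert value, mild-then-alert patients are placed correctly. The illustrative range is 0% to about 85% of alert-level ALAT patients, depending on the reading and on assumed distributions that the protocol neither gives nor rules out.

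The consequence is confined to a descriptive safety table. No test and no primary conclusion depends on it. It is worth correcting because the replacement is clearly better and costs almost nothing.

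**What to change.** In section 14.1.4, Clinical laboratory evaluation, replace the shift to first event by: shift tables from baseline to the worst value under treatment, separately for the low and high directions, using scheduled and unscheduled samples. If timing is of interest, time to the first alert value may be added.

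Cost: one sentence and minor programming. No new data are needed, and no sampling or treatment rule changes. The downside is that the tables will show slightly more abnormal values in both arms.

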| Study period:
- Study duration for the participant: 1 year + run-in (4 weeks)
- Study completion date: 1 st February 2008                                                                                                                                                                                                                                                                                                                                                                                                                                                                                                                                                                                                                                                                                                             |                                                                | Study development phase: III      |
| Objectives: The primary objective is to demonstrate the non-inferiority of the combination benfluorex plus sulfonylurea compared to the combination pioglitazone plus sulfonylurea on the evolution of HbA1c (main criterion) over one year of treatment. Both benfluorex and pioglitazone will be administered at optimal dosage for the treatment of type 2 diabetic patients insufficiently controlled on sulfonylurea monotherapy.
The secondary objective is to demonstrate the superiority of benfluorex combined with sulfonylurea compared to pioglitazone combined with sulfonylurea on Low Density Lipoprotein (LDL) cholesterol level.
The other secondary objectives are to assess the efficacy on Fasting Plasma Glucose (FPG), the safety profile, the cardiovascular risk profile and the economic balance of the two treatments. |                                                                |                                          |

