Thiazolidinediones (TZD) represent a new class of insulin-sensitizing agents which activates nuclear receptors called peroxisome proliferators-activated receptors (PPAR) $\gamma$ , which are expressed predominantly in adipose tissue and regulate the transcription of genes involved in adipocyte differentiation, and glucose and lipid metabolism. Thiazolidinediones are recommended in combination therapy when sulfonylurea in monotherapy at maximum tolerated dose has failed to obtaining blood glucose control. Thiazolidinediones expand plasma volume and may cause fluid retention with anaemia, weight gain, and peripheral oedema, leading to contraindication to patients with cardiac failure as well as mildly elevated liver enzymes.

Benfluorex is an agent that possesses both anti-hyperglycaemic and hypolipidaemic properties. Its main action in diabetic patients is to improve insulin sensitivity, as demonstrated in 3 double-blind, placebo-controlled studies using the euglycaemic (7;8) or the isoglycaemic (9) clamp technique. Its mode of action is different from that of metformin or thiazolidinediones (10;11). Benfluorex improves muscle insulin resistance with an increase in the glucose transporter GLUT-4 (12;13) and in glucose oxidation (14). It also decreases hepatic glucose output with an effect on glucose neogenesis through an inhibition of phosphoenol pyruvate carboxykinase (15;16) with a concomitant decrease in mitochondrial

$\beta$ -oxidation of fatty acids through an inhibition of carnitine palmityl transferase I (11). Benfluorex has no effect on basal or stimulated insulin secretion in diabetic rats (17;18).

Although benfluorex has been used in the treatment of type 2 diabetes for many years, its efficacy in combination with other oral antidiabetic agents has mostly been demonstrated in small-scale studies (19;20). Its efficacy in type 2 diabetes in combination with sulfonylureas versus placebo was recently confirmed by the large scale study CL3-00780-146 in which a decrease of HbA1c of –1% versus placebo was observed. Moreover, a benefit or a neutral effect was observed on cardiovascular risk factors such as weight, blood pressure, triglycerides and LDL cholesterol.

Given the complementary mode of action of benfluorex and sulfonylureas, the former acting on peripheral insulin action, and the latter on insulin secretion, i.e. the two main processes altered in type 2 diabetes, benfluorex should be of particular interest in this combination.

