## **7. STUDY OBJECTIVES AND PURPOSE**

The purpose of this study is to compare the efficacy and the safety profile of benfluorex and pioglitazone in type 2 diabetic patients, not optimally controlled on sulfonylurea, over 1 year.

The primary objective will be to demonstrate the non-inferiority of the combination sulfonylurea plus benfluorex compared to the combination sulfonylurea plus pioglitazone on the evolution of HbA1c.

Both benfluorex and pioglitazone will be administered at optimal dosage for the treatment of type 2 diabetic patients insufficiently controlled on sulfonylurea monotherapy.

The main secondary objective is to demonstrate the superiority of benfluorex combined with sulfonylurea compared to pioglitazone combined with sulfonylurea on LDL cholesterol level.

The other secondary objectives will be to evaluate and compare over 1 year both combination therapies on the following:

- Fasting Plasma Glucose evolution.
- Insulin Resistance assessed by homeostatic model assessment (HOMA-IR).
- Cardiovascular risk profile.
- Safety and acceptability.
- Cost of the two treatments through an economic balance.

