**Efficacy criteria:**

- Low Density Lipoprotein (LDL) cholesterol assessed by direct method.
- Fasting Plasma Glucose (FPG) levels.
- Insulin, Insulin Resistance assessed by homeostatic model assessment (HOMA-IR).
- Markers of the cardiovascular risk:
  - Other fasting lipids parameters: total cholesterol, High Density Lipoprotein (HDL) cholesterol, triglycerides, non-HDL cholesterol, Apo A1, Apo B and LDL particle size (optional),
  - Waist circumference.
- Inflammatory factor : high sensitive C Reactive Protein (hsCRP).

**Safety and acceptability profile** will be assessed by:

- Adverse events including oedemas and cardiovascular events (for all suspected events of cardiac origin, a cardiological examination will be performed).
- Hypoglycaemia events classified according to the EMEA guidelines in major, minor and suggestive episodes.
- Physical examination including body weight.
- Cardiological examination
- N-Terminal pro-Brain Natriuretic Peptide (NT-proBNP) (23; 24).
- Laboratory centralised examinations: standard biochemistry (including hepatic parameters focusing on ALAT and lactic acid) and haematology (including haemoglobin and haematocrit follow-up).

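### Section 7 sets out to compare the safety profile of the two arms, but section 14.1.4 commits to no formal between-arm estimate for weight, blood pressure, oedema, hypoglycaemia or cardiovascular events

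*Protocol*

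**What the plan says.** **Objectives.** The opening sentence of section 7 gives the purpose as a comparison of efficacy and of safety profile between the two drugs. It then continues: "The other secondary objectives will be to evaluate and compare over 1 year both combination therapies on the following". The list that follows includes "Cardiovascular risk profile" and "Safety and acceptability". The study summary sheet is softer on the same objectives, which there are "to assess the efficacy on Fasting Plasma Glucose (FPG), the safety profile, the cardiovascular risk profile and the economic balance of the two treatments".

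**Classification.** Section 8.1 places "Markers of the cardiovascular risk" among the secondary efficacy criteria: the other lipids, Apo A1, Apo B, LDL particle size and waist circumference. Section 14.1.1 keeps the same variables as secondary criteria. Weight, BMI, blood pressure and heart rate are safety criteria in that section. The background (section 6), reporting an earlier placebo-controlled study, speaks of "cardiovascular risk factors such as weight, blood pressure, triglycerides and LDL cholesterol".

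**Analysis (section 14.1.4).** Secondary efficacy criteria receive the main general linear model, with treatment difference, standard error and 95% confidence interval. For the safety criteria, "Vital signs will be described by group using value at the visit, last post-baseline value and change between baseline and last post-baseline value". The study summary sheet counts weight as a vital sign. Under the heading for hypoglycaemia, oedema and cardiovascular events the whole text is: "A survival analysis will be performed in case of sufficient number of events". Adverse events are tabulated by System Organ Class, Preferred Term and treatment group.

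**The concern.** The stated aim and the stated method do not match. Section 7 asks for a comparison of safety, while section 14.1.4 offers separate descriptions of each arm. For the three event types singled out by name, the only inferential analysis depends on a count that this document does not define.

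The contrast matters to the trial's own rationale. Section 6 describes thiazolidinediones as liable to cause fluid retention, weight gain and oedema, and puts benfluorex forward as an alternative. Readers will want to know how far the arms differ on those outcomes and how precisely the difference is known. Under the plan as written they would subtract two unadjusted means or percentages themselves. Waist circumference, a closely related measure, would come with a baseline-adjusted difference and its interval.

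**Working it through.** **1. Objective against method**

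| Variable | Objective in section 7 | Class in 8.1 and 14.1.1 | Between-arm estimate committed in 14.1.4 |
|---|---|---|---|
| LDL cholesterol | Main secondary | Efficacy | Difference, SE, 95% CI, superiority test |
| Other lipids, Apo A1, Apo B, waist | Cardiovascular risk | Efficacy | Difference, SE, 95% CI |
| Weight, blood pressure | Safety | Safety | None; described by group |
| Oedema, hypoglycaemia, cardiovascular events | Safety | Safety | Survival analysis if events suffice (number not stated); otherwise by-arm description |

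The gap is therefore confined to the last two rows.

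**2. The plan's own sample size.** Section 14.2 gives SD 1.5%, margin 0.40%, true difference up to 0.05%, one-sided 2.5% and power 95%:

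n = 2 × (1.960 + 1.645)² × 1.5² / (0.40 − 0.05)² = 477.4, so 478 per group. The t-based version gives 479, as stated. No figure in the plan is in dispute here. Section 14.2 also supplies the roughly 500 included per group, used below as an approximation to the Safety Set.

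**3. Precision for weight and systolic blood pressure.** The half-width is 1.96 × SD × √(2/500) = 0.124 × SD. The protocol gives no SD for either variable, so the SDs are assumptions.

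- Weight, SD 3, 4, 5 kg: ±0.37, ±0.50, ±0.62 kg.
- Systolic pressure, SD 12, 15, 18 mmHg: ±1.5, ±1.9, ±2.2 mmHg.

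For scale, Appendix 5 (its section 4.8) reports a mean gain of 2.8 kg over a year when pioglitazone is added to a sulfonylurea. That is a change within one arm, not a difference from benfluorex.

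**4. Oedema.** Appendix 5 gives 6–9% on pioglitazone and 2–5% in comparator groups treated with sulfonylurea or metformin. Assume, for illustration only, that benfluorex behaves like those comparators. With 500 per arm, the half-width is 1.96 × √[p₁(1−p₁)/500 + p₂(1−p₂)/500], and power is for a two-sided 5% test.

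| p₁ vs p₂ | Expected events | Difference (points) | Half-width (points) | Power |
|---|---|---|---|---|
| 6% vs 5% | 55 | 1 | 2.8 | 10% |
| 9% vs 5% | 70 | 4 | 3.2 | 70% |
| 6% vs 2% | 40 | 4 | 2.4 | 90% |
| 9% vs 2% | 55 | 7 | 2.8 | over 99% |

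Power depends almost wholly on which rates are assumed. The interval width is stable at 2.4 to 3.2 points, so an interval would be informative throughout this range.

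**The case against.** The case on the other side has four parts.

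- **Cardiovascular risk is covered.** A reader might infer that the trial gives no between-arm estimate for its cardiovascular risk objective. The documents do not support that. Section 8.1 says which variables are the risk markers, and section 14.1.4 gives them a difference with SE and 95% CI. The sentence in section 6 that names weight and blood pressure describes an earlier study and does not reassign them here. This stands in full.
- **The harms are reported in any case.** A reader might also infer that safety cannot be compared from the output, or that reporting of key harms depends on the data. Only the survival analysis is conditional. The study summary sheet promises descriptive statistics for oedema, cardiovascular events and hypoglycaemia without condition. Section 14.1.2 fixes n, mean and SD, or number and percentage. A crude difference and an unadjusted interval can be computed from those. This stands too; what is missing is a committed, adjusted or formal estimate.
- **Descriptive safety reporting is common, and detail belongs in the SAP.** Section 14.1 leaves implementation to a SAP not shown here, and the threshold for a sufficient number of events could properly be set there. This stands in part. Section 14.1 also requires the SAP to follow the principal features of the protocol. On these variables the protocol is not silent, and a SAP could satisfy it without comparing the arms.
- **The summary sheet does not say compare.** This is true, but section 7 does, both in the purpose sentence and in the lead-in to the secondary objectives. The two places need to agree.

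**Conclusion.** The point holds in a narrow form and is minor. Section 7 promises a comparison of safety. Section 14.1.4 commits to description by arm for weight and blood pressure, and to a conditional analysis with an undefined trigger for oedema, hypoglycaemia and cardiovascular events. The primary HbA1c analysis, the LDL cholesterol test and the section 8.1 risk markers are untouched.

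The weight and blood pressure half-widths rest on assumed SDs and on about 500 patients per arm in the Safety Set. The oedema figures rest on Appendix 5 rates whose comparators are sulfonylurea and metformin. A single power figure, such as the roughly 80% obtained from the range midpoints of 7.5% against 3.5%, should not be quoted alone, because the documents support anything from about 10% to over 99%. The calculations show only that usable intervals are available from data the trial already collects.

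**What to change.** In section 14.1.4, under Safety:

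- Analyse change from baseline to last post-baseline value in body weight and in sitting systolic and diastolic blood pressure with the general linear model already used for efficacy (own baseline and country as covariates). Report the treatment difference, SE and 95% CI.
- For oedema, hypoglycaemia and cardiovascular events, report the between-arm difference in the proportion of patients affected with its 95% CI whatever the count, using an interval method that remains valid with few events.
- Keep the survival analysis as an addition. Its minimum number of events can be set in the SAP before the blind is broken.
- Label all these intervals as not adjusted for multiplicity.

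The cost is a few extra tables on data already scheduled at each visit. The downside is a set of unadjusted intervals that could be over-read, which the label addresses. Rewording section 7 to match the study summary sheet would also remove the mismatch, but it would give up a comparison that the study names as part of its purpose.
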